## Abstract

**Introduction:**

The improvements in short-term outcome after severe trauma achieved through early resuscitation and acute care can be offset over the following weeks by an acute systemic inflammatory response with immuneparesis leading to infection, multiorgan dysfunction/multiorgan failure (MOF) and death. Serum levels of the androgen precursor dehydroepiandrosterone (DHEA) and its sulfate ester DHEAS, steroids with immune-enhancing activity, are low after traumatic injury at a time when patients are catabolic and immunosuppressed. Addressing this deficit and restoring the DHEA(S) ratio to cortisol may provide a range of physiological benefits, including immune modulatory effects.

**Objective:**

Our primary objective is to establish a dose suitable for DHEA supplementation in patients after acute trauma to raise circulating DHEA levels to at least 15 nmol/L. Secondary objectives are to assess if DHEA supplementation has any effect on neutrophil function, metabolic and cytokine profiles and which route of administration (oral vs sublingual) is more effective in restoring circulating levels of DHEA, DHEAS and downstream androgens.

**Methods and analysis:**

A prospective, phase II, single-centre, cross-sectional, randomised study investigating Dehydroepiandrosterone supplementation and its profile in trauma, with a planned recruitment between April 2019 and July 2021, that will investigate DHEA supplementation and its effect on serum DHEA, DHEAS and downstream androgens in trauma. A maximum of 270 patients will receive sublingual or oral DHEA at 50, 100 or 200 mg daily over 3 days. Females aged ≥50 years with neck of femur fracture and male and female major trauma patients, aged 16–50 years with an injury severity score ≥16, will be recruited.

**Ethics and dissemination:**

This protocol was approved by the West Midlands – Coventry and Warwickshire Research Ethics Committee (Reference 18/WM/0102) on 8 June 2018. Results will be disseminated via peer-reviewed publications and presented at national and international conferences.

**Trial registration:**

This trial is registered with the European Medicines Agency (EudraCT: 2016-004250-15) and ISRCTN (12961998). It has also been adopted on the National Institute of Health Research portfolio (CPMS ID:38158).

**Trial progression:**

The study recruited its first patient on 2 April 2019 and held its first data monitoring committee on 8 November 2019. DHEA dosing has increased to 100 mg in both male cohorts and remains on 50 mg in across all female groups.

Strengths and limitations of this studyIdentify the dose and route of administration needed to normalise dehydroepiandrosterone levels in a cohort that are known to have low levels, both habitually and post-traumatic injury.The rapid turnaround time from bedside to bench and bench to interim analysis will minimise inappropriate dosing and public money expenditure on ineffective doses.This swift analysis will limit patient exposure to insufficient dosing and unnecessary specimen collection.A study limitation could be its single-site design; however, this will facilitate collecting sensitive immunological samples.

## Introduction

The improvements in short-term outcome after severe trauma achieved through early resuscitation and acute care are offset over the following weeks by an acute systemic inflammatory response with immuneparesis leading to infection, multiorgan dysfunction/multiorgan failure (MOF) and death.^1 2^ The combination of excessive pro-inflammatory and anti-inflammatory responses impairs the rehabilitation phase of trauma, including wound healing, physical and emotional recovery.^3^ Upregulation of glucocorticoid biosynthesis promotes a catabolic state, lasting several weeks and is associated with a significant reduction in muscle mass.^4^

Analysis of gender differences in trauma has shown that women, particularly those under 30 years of age, have fewer infections and a better outcome from sepsis than men.^5 6^ The protective effects of oestrogens on immune cells and organ function highlight the potential role of sex hormones in modulating trauma-related immune dysfunction.^7^ Cellular immunity is also influenced by hormone production, and members of our group have shown that the adrenal response to stress, specifically the ratio of cortisol to dehydroepiandrosterone sulfate (DHEAS), is linked to neutrophil bactericidal function, specifically superoxide production.^8 9^

Dehydroepiandrosterone (DHEA) and its sulfate ester DHEAS are the most abundant steroids in the human circulation; DHEA is a precursor of sex hormones modulating several physiologic processes including metabolism, muscle protein synthesis and cardiovascular function.^10 11^ DHEA is converted to active androgens in peripheral target cells including immune cells^12^ and is also converted to DHEAS by the action of DHEA sulfotransferase (SULT2A1).^13^ We have shown that DHEA sulfation is downregulated in acute systemic inflammatory response syndrome (SIRS) and sepsis.^14^ Hazeldine *et al*^15^ reviewed the numerous immune effects of DHEA highlighting how DHEAS, but not DHEA, enhances neutrophil superoxide generation via a protein kinase C mediated pathway, a vital immune response in fighting bacterial infections.^8^

The roles of DHEA and DHEAS in severe injury are relatively unexplored. The majority of studies focus on cortisol responses,^16^ whereas our data suggest that it is the cortisol:DHEAS ratio post-trauma that has a superior prognostic ability.^17 18^ Although critical for survival, prolonged hypercortisolaemia is known to be detrimental in part due to its immunosuppressive effects.^19^ This intra-adrenal shift causes decreased levels of circulating testosterone and oestrogen, resulting in rapid lean body mass loss,^20^ in addition to increased susceptibility to infection and sepsis.^21^ Correcting the cortisol:DHEA or cortisol:DHEAS ratio via the administration of DHEA has yet to be undertaken in traumatically injured patients despite DHEA and DHEAS being below the reference ranges for 6 weeks and 6 months postinjury, respectively.^4^

DHEA is subject to first-pass metabolism in healthy individuals, which in turn may lead to a non-physiological metabolism after an oral dose.^22^ Bypassing first-pass metabolism using a sublingual or buccal preparation^23^ should improve the bioavailability of DHEA.^24 25^ Previous studies in healthy older people have shown that supplementation with 50 mg DHEA orally once daily can restore both serum DHEA and DHEAS levels to that of men and women in the third decade of life.^22 26^ Furthermore, the current literature suggests that DHEA supplementation may be beneficial for immune function and could extend to bone remodelling, muscle composition, psychological and neurological improvements.^27^

This study will seek to estimate the optimal dose and route of administration of DHEA in trauma patients and increase serum levels of DHEA and DHEAS to those seen in healthy adults. We also aim to find the optimal dose to enhance immune function, as demonstrated through changes in neutrophil phagocytosis and reactive oxygen species (ROS) production. The pilot data generated from the study is necessary to develop the protocol for a randomised controlled trial that will determine whether DHEA supplementation may improve outcomes in injured patients.

## Rationale

### Justification of the patient population

Despite improvements in short-term outcomes from traumatic injury via aggressive early resuscitation and acute care, over 5 million people worldwide die each year from serious injury.^28^ With improved prehospital medicine mitigating the immediate threats to life it is the following weeks after traumatic injury that has seen the dysregulated SIRS in susceptible patients. The SIRS response is accompanied by a compensatory anti-inflammatory response (CARS)^29^ to restore homeostasis. SIRS and CARS may progress to the persistent inflammation, immunosuppression and catabolism syndrome (PICS).^30 31^ PICS further compounds the insult from the initial injury and results in an increased risk of infection, MOF and late deaths.^1 2^ Therefore, strategies to mitigate these detrimental outcomes for patients are needed in the short-term, medium-term and long-term care of trauma patients.

The young trauma cohort will be recruited alongside a cohort of older (≥50 years old) female patients who have sustained a hip fracture at the neck of femur (NOF). According to the National Hip Fracture Database (2018), the NOF burden on the UK economy is estimated to be around £1 billion per annum.^32^ This considerable cost is set to rise as the population ages. By the age of 40 years, decreasing serum levels of DHEA and DHEAS are observed in both sexes,^33 34^ a phenomenon sometimes referred to as ‘adrenopause’. Circulating levels of DHEA and DHEAS are lower in women than in men; however, in postmenopausal women, adrenal androgens are a source of almost all active oestrogens.^35^ To the best of our knowledge, there has been no traumatic injury or NOF interventional studies supplementing DHEA or DHEAS, despite its therapeutic potential in the immediate to longer term care of the young and aged trauma patient. In this pilot study, we will recruit a female NOF cohort as well as a young adult trauma cohort with both male and female patients presenting at the major trauma centre (MTC) and intensive care unit (ICU) at Queen Elizabeth Hospital, Birmingham (QEHB), UK.

### Choice of treatment

The DHEA doses chosen in this study (50 mg, 100 mg and 200 mg) were selected based on in vivo studies that demonstrated these doses to be both safe and effective at raising the levels of DHEA to that of healthy young adult levels.^36^ DHEA is at its highest in the third decade of life. After which there is a steady decrease over the life course in both males and females. These doses have also previously been used in adrenal insufficiency,^37^ older people^38^ and young males^39^ and females,^23^ causing transient hyperandrogenism with acne being the most frequently reported side effect.^40 41^ DHEA is activated to downstream androgens by stepwise conversion catalysed by several steroidogenic enzymes. However, we do not know whether the expression and activity of these enzymes are affected by major trauma and inflammation. There is evidence that inflammation and trauma affect DHEA sulfation^4 14^ and may shift the conversion of DHEA to a higher rate of androgen activation.

Trauma and inflammation can impact adversely on gut absorption^42^ and hepatic first-pass metabolism.^43^ Therefore, we have chosen to administer DHEA as a sublingual preparation. Sublingual administration is commonly used by nursing staff in the ICU context, especially in those patients who have contraindications to oral administration or by patients wishing to self-administer.^44^

## Objectives

### Primary objective

The primary objective of this study is to establish the daily dose of DHEA that restores serum DHEA levels to at least 15 nmol/L, that is, the mid-healthy adult reference range, in trauma and hip fracture patients after 3 days of supplementation.

### Secondary objective

Secondary objectives include observing the effect of single and multiple DHEA doses on circulating DHEA, DHEAS and downstream androgens. Additionally, we will investigate whether the route of DHEA administration (oral vs sublingual) modulates the profile of circulating DHEA. This will be determined by assessing the efficacy of each route via statistical modelling. The immune response to the DHEA supplementation will be assessed as a marker of potential clinical relevance.

## Methods

### Trial design

A prospective, phase II, single-centre, cross-sectional, randomised study investigating Dehydroepiandrosterone supplementation and its Profile in Trauma (ADaPT) trial conducted in male and female adult trauma patients and older females who have suffered neck of the femur fracture. This is a single-site study with patients recruited from QEHB. Three doses of DHEA will be investigated in this trial: 50, 100 and 200 mg, each administered once daily for 3 days via either oral or sublingual tablets. The trial has an adaptive design in order to answer both the primary and secondary objectives, with regular interim analysis to minimise the investigation of inactive doses. The trial consists of two components. The first component of the trial is to determine the dose of DHEA needed to sufficiently raise serum DHEA levels to at least 15 nmol/L after 3 days of DHEA administration. Based on previous work, 15 nmol/L has been selected as this is the lower acceptable level of DHEA observed in healthy young adults. Our recent analysis of the steroid response to trauma has shown that DHEA levels were very low and often undetectable for several weeks after trauma.^4^ The second component of the trial is to investigate if DHEA will enhance neutrophil function. The study was approved by The Medicines and Healthcare products Regulatory Agency (MHRA) for the use of DHEA as an investigational medicinal product (IMP). Ethical approval was obtained from the West Midlands Research Ethics Committee (Reference 18/WM/0102). The trial will be conducted in accordance with the Declaration of Helsinki (World Medical Association 2008). Figure 1 summarises the patient pathway of the trial. The protocol (V.5.0, 28 June 2019) has been prepared in accordance with the Standard Protocol Items: Recommendations for Interventional Trials (SPIRIT) guidelines.^45^

**Figure 1 F1:**
[figure not shown]
A trial flow chart describing the patient journey in through the ADaPT study. * Due to the nature of the injury, informed consent can be sought from a professional legal representative or personal legal representative if the patient does not have capacity. Consent from the patient will be obtained at the earliest opportunity by research team members. **Twenty-four-hour blood and consent will only be collected within 24 hours of injury. The omission of this sample collection does not render a patient unevaluable. ADaPT, A prospective, phase II, single-centre, cross-sectional, randomised study investigating dehydroepiandrosterone supplementation and its Profile in Trauma; DHEA, dehydroepiandrosterone.

### Patient selection

A maximum of 270 patients will be enrolled across three patient groups (young male trauma, young female trauma and female hip fracture). These trauma patient groups have been selected due to the immuneparesis effects caused by the acute systemic inflammatory response that follows severe trauma. The hip fracture group was selected as they have low serum DHEA and DHEAS due to adrenopause, and there are several papers showing an association between HPA axis activity measures and outcomes in these patients.^9 18 46 47^ Patients admitted to QEHB will all be prescreened and assessed for eligibility. Patients will be screened between 07:00 and 20:00, 7 days a week. Potential participants will have an assessment of their medical history and current trauma injury, and the eligible patients will be recruited. The eligibility criteria have been split into trauma patients and hip fracture patients (box 1). The study will not exclude NOF patients with dementia where supplementation is currently being tested in the prevention and treatment of age-related cognitive impairment without deleterious effects.^48^

Box 1Patient inclusion and exclusion criteriaTrauma patients inclusion criteria:Aged 16–50 years of age.Severely injured trauma patient (injury severity score (ISS) ≥16 and ≤50).Admitted to University Hospital Birmingham within 6 days of trauma.Anticipated to be an inpatient for the 12-day trial period.Trauma patients exclusion criteria:Ages <16 or >51.ISS <16 or >50.Isolated brain injury.Unlikely to survive the study period.Known hormone sensitive malignancy.Known prostatic hypertrophy (M).Female patients taking hormone replacement therapy (HRT) medication or oral contraceptives.Intake of any drugs that interfere with adrenal function in the last 3 monthsPre-existing liver impairment or chronic liver failure.Previous or current malignancy or invasive cancer diagnosed within the past 3 years except for adequately treated basal cell and squamous cell carcinoma of the skin and in situ carcinoma of the uterine cervix.Pregnant and/or breastfeeding females (women of childbearing potential to complete serum pregnancy test).Known hypersensitivity to the active substance or excipient.Known thromboembolic events in the last 12 months and any predisposition to thrombosis, e.g, Factor V Leiden.Hip fracture patients inclusion criteriaAged 50 years and older.Female.Neck of femur fracture.Admitted to University Hospital Birmingham within 6 days of fracture.Anticipated to be an inpatient for the 12-day trial period.Hip fracture patients exclusion criteria<50 years old.Unlikely to survive the study period.Previous or known hormone sensitive malignancy.Intake of any drugs that interfere with adrenal function in the last 3 months.Pre-existing liver impairment or chronic liver failure.Previous or current malignancy or invasive cancer diagnosed within the past 3 years except for adequately treated basal cell and squamous cell carcinoma of the skin and in situ carcinoma of the uterine cervix.Pregnant and/or breastfeeding (women of childbearing potential to complete serum pregnancy test).Known hypersensitivity to the active substance or excipient.Females on HRT medication.Known thromboembolic events in the last 12 months and any predisposition to thrombosis e.g. Factor V Leiden.

### Randomisation

Patients who meet the eligibility criteria and provide consent are randomised to receive DHEA via either oral tablets or sublingual tablets once daily for 3 days using a 1:1 randomisation ratio. With 3 populations of patients (male trauma, female trauma and female hip fracture) and two routes of administration, there will be six groups in total. Randomisation will take place using a secure web-based tool. Nursing and medical staff will use the Clinical RESearch Tool (CREST), developed at University Hospitals Birmingham Foundation Trust (UHB), to randomly assign patients and provide an anonymised electronic case report form (CRF), for trial management, data collection and adverse event reporting. The prevailing dose of DHEA (50, 100 or 200 mg) for administration in a group will be adapted in response to sequential analysis of interim outcomes. Each group will have its own dose. Blinding is not possible as the difference in DHEA delivery method is evident to both the clinician and the participant. If a contraindication to oral or the sublingual route present prior to commencing the study intervention, forced randomisation will occur.

### Study intervention

The supplementation of DHEA will commence in the second week after injury, which has previously been shown to be a time when trauma patients become maximally unwell as a result of sepsis and MOF.^49^ Additionally, this time point has been selected to optimise patient recruitment from both the NOF cohort and trauma patients (median stay 18 days and 13 days, respectively) both DHEA and DHEAS levels post-injury.^50^ Recruiting an in-hospital cohort provides an opportunity to monitor patients and assess the impact that this class C controlled drug has on the serial steroid profile and immune function during a period of vulnerability over 3 days of administration.

### Participant timeline

The trial intervention will occur over 3 days, during the first 12 days while patients are at QEHB. Three doses of DHEA will be investigated in all patients, and dosing will occur on days 8, 9 and 10 only. All cohorts will begin the study on 50 mg, and the dose administered to the next eligible patient to be included within a cohort will be escalated when interim analysis determines if the primary objective has been reached. At no point will any patient escalate once they have been allocated a dose of DHEA.

### Dose escalation

Dose escalation for the DHEA restoration part of the trial is dependent on the serum DHEA levels. A dose that restores serum DHEA to ≥15 nmol/L (referred to as ‘normalise DHEA’) is sought in at least 13 out of 15 patients or approximately 85% of patients. The decision to escalate dose in a cohort will be driven in the main by the outcomes of the patients in that cohort and escalation will occur independently for each cohort. However, valuable additional information will be garnered from the outcomes of patients in other cohorts. Flexible information sharing across related groups will be achieved using hierarchical regression models. The requirement for 13 out of 15 patients to normalise in the final effective dose is based on what was judged to be clinically important and thus would warrant investigation of the chosen dose of DHEA in a confirmatory phase III trial to ascertain superiority of outcomes compared with standard of care.

To minimise the investigation of inactive doses, we propose an analysis of each dose level in each cohort after 3 to 5 evaluable patients have been assessed. It will be taken as evidence that the normalisation rate is too low and that the dose should be increased if: any patient fails to normalise (where n=3) or more than one patient fails to normalise (where n=4 or 5). This rule-based analysis will provide an early opportunity to escalate in search of a more promising dose when a probabilistic analysis will likely be underinformed due to the small sample size. If the requisite number normalise, recruitment will continue in that cohort at that dose-level up to a maximum of 15.

Once an effective dose has been established to normalise DHEA levels within a group and at least 15 patients have completed it, the DHEA will be escalated to the next dose to satisfy the second component of the trial and to determine whether further increases in DHEA supplementation will enhance immune function. The immune response component will focus on neutrophil phagocytosis and ROS production that will involve fewer research samples. Fifteen patients (within a cohort) will complete the immune response part of the trial at each subsequent dose escalation. If 50 mg is established to be sufficient to normalise DHEA, the dose will be escalated twice to investigate whether 100 mg or 200 mg is optimal for increasing the immune response. Both 100 mg and 200 mg have safely been used in previous studies,^51 52^ but this has not been addressed in the context of trauma. Each group will be escalated independently of each other (figure 2).

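### After the 3-to-5-patient look, no rule is stated for a third failure, although three failures already put 13 out of 15 out of reach

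*Protocol article*

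**What the plan says.** All of this comes from the protocol article.

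- **Criterion (Dose escalation).** A dose that normalises serum DHEA "is sought in at least 13 out of 15 patients or approximately 85% of patients". The same section refers to "The requirement for 13 out of 15 patients to normalise in the final effective dose".
- **Early look (Dose escalation).** The plan proposes "an analysis of each dose level in each cohort after 3 to 5 evaluable patients have been assessed". One failure among 3 patients, or two among 4 or 5, counts as evidence that the dose should be raised.
- **After the look (Dose escalation).** If enough patients normalise, "recruitment will continue in that cohort at that dose-level up to a maximum of 15". No failure count or probability threshold is given between the look and 15.
- **Aims.** Trial design describes an adaptive trial "with regular interim analysis to minimise the investigation of inactive doses". The strengths and limitations text after the abstract adds: "This swift analysis will limit patient exposure to insufficient dosing and unnecessary specimen collection".
- **Further review.** The Interim analysis section ties interim analyses to a dose-escalation decision in a cohort and refers back to the rules above. The DMC section has the committee advise on those rules and lets it ask for extra meetings. The primary outcome analysis offers hierarchical models in support of dose decisions, without a cut-off.

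**The concern.** A cohort that passes the look can still collect failures. Once it has three, no later outcome can bring it to 13/15, so the verdict on that dose is settled. The text then gives no instruction except that recruitment goes on, with 15 as the ceiling.

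The stated rules are also uneven. Two failures in the first five patients lead to escalation. One failure in the first five followed by two more, which is three in seven, leads to nothing that is written down.

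At stake are patients entering a dose level that can no longer meet the trial's own criterion, and recruitment time at a single centre. The first DMC review, on 8 November 2019, covered 16 patients about seven months after the first was recruited.

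**Working it through.** **The plan's own figures.** Maximum sample size: 6 groups × 15 patients × 3 doses = 270, as stated. Criterion: 0.85 × 15 = 12.75, rounded up to 13, and 13/15 = 86.7%, which agrees with the approximate 85%.

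**When 13/15 is lost.** Thirteen of 15 allows at most two failures. Three failures leave at most 12/15 = 80%.

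**Earliest third failure.** A look at 3 is passed with no failures, so the third can come at patient 6. A look at 4 is passed with at most one failure, so two more can bring it to patient 6. A look at 5 is also passed with at most one, so the earliest is patient 7. Places left: 15 − 6 = 9, or 15 − 7 = 8.

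**How often, and how many places.** The true normalisation rate p is an assumption. I use 60% and 70% for a dose that falls short, and 85% because it is the plan's own target. Let m be the size of the look (3, 4 or 5), c the failures allowed at it (0, 1, 1) and q = 1 − p.

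- P(pass look) = Σ over f ≤ c of C(m,f) q^f p^(m−f)
- P(pass and reach 13/15) = Σ over f ≤ c of C(m,f) q^f p^(m−f) × P(Bin(15−m, q) ≤ 2−f)
- P(third failure by 15, given pass) = 1 − P(pass and reach 13/15) / P(pass look)
- Mean places after the third failure, per cohort starting at the dose = Σ over n of (15 − n) × P(pass and third failure at patient n)

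Worked case, m = 5 and p = 0.7:

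- P(pass) = 0.7^5 + 5 × 0.3 × 0.7^4 = 0.168 + 0.360 = 0.528.
- P(pass and reach 13/15) = 0.168 × 0.383 + 0.360 × 0.149 = 0.118.
- P(third failure | pass) = 1 − 0.118/0.528 = 0.776.
- Given a third failure, a mean of 4.21 places remain, so the mean per starting cohort is 0.528 × 0.776 × 4.21 = 1.73.

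Exact enumeration for all permitted looks:

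| Look at | Assumed rate | Passes look | Third failure by 15, given pass | Mean places left, given third failure | Mean per starting cohort |
|---|---|---|---|---|---|
| 3 | 60% | 0.216 | 0.917 | 5.20 | 1.03 |
| 3 | 70% | 0.343 | 0.747 | 4.25 | 1.09 |
| 3 | 85% | 0.614 | 0.264 | 3.07 | 0.50 |
| 4 | 60% | 0.475 | 0.946 | 5.80 | 2.61 |
| 4 | 70% | 0.652 | 0.813 | 4.83 | 2.56 |
| 4 | 85% | 0.890 | 0.340 | 3.53 | 1.07 |
| 5 | 60% | 0.337 | 0.926 | 5.02 | 1.57 |
| 5 | 70% | 0.528 | 0.776 | 4.21 | 1.73 |
| 5 | 85% | 0.835 | 0.309 | 3.14 | 0.81 |

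If all six cohorts had the same rate of 60-70% at a dose, the total for that dose would run from 6 × 1.03 = 6.2 to 6 × 2.61 = 15.7 patients. The shared rate is a further assumption.

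All these figures assume that recruitment does run to 15. They are upper bounds on what a rule could save. Patients may enter within 6 days of injury but are dosed on days 8 to 10, so some will already be enrolled or awaiting assay when the third failure is known.

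**The case against.** A reader might infer that the plan obliges a cohort to recruit to 15 after a third failure. It does not. Fifteen is a ceiling, and no section requires continuation once 13/15 is lost. The article promises regular interim analysis. It justifies the rule-based look by the weakness of a probabilistic analysis at small numbers, which suggests that model-based review follows as numbers grow. It also lets the DMC meet more often. This stands, and it limits the point to a missing statement. None of these routes carries a threshold, however, and none names the third failure as an occasion for review.

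The dose-escalation flow chart (Figure 2) is not visible, and the article condenses protocol V.5.0. A rule may exist there, so its absence from the trial cannot be asserted. But the article prints the early rule down to failure counts at 3, 4 and 5 and then says only that recruitment goes on. On its face the rule stops short.

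A reader might also infer that patients after the third failure are wasted. They are not. The Sample size section chose 15 to give information on the primary outcome at each dose in each group, and those patients still feed the Wilson intervals and the pooled model. A dose ending at 12/15 is also hardly inactive. Both arguments are fair, and they are reasons to state the intention either way.

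**Conclusion.** The point holds as a gap between the continuation rule, the 13/15 criterion and the stated aims. As printed, up to 9 further patients (look at 3 or 4) or 8 (look at 5) can enter a dose level that can no longer meet its criterion. That three failures rule out 13/15 is certain.

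The average size depends on assumed rates and on which look is used. At 60-70% it is about 1.0-1.1 patients per starting cohort for a look at 3, 2.6 for a look at 4, and 1.6-1.7 for a look at 5. At 85% it is 0.5-1.1. All are upper bounds. The effect is modest but worth a sentence, since the article presents sparing patients insufficient dosing as a strength of the design.

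**What to change.** Reconcile the continuation rule in Dose escalation with the 13/15 criterion and the stated aims. One sentence would do: at the third failure to normalise among evaluable patients at a dose level, 13/15 is recorded as not attainable, and an interim analysis and DMC review of that cohort is triggered. The dose decision stays with the DMC and the trial team. If recruitment to 15 is intended for estimation, say that instead and explain how it fits the aims. If V.5.0 or Figure 2 already holds such a rule, the article should report it.

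Recording a third failure leaves the 13/15 verdict unchanged. If recruitment then ends early, there are two costs:

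- There are fewer observations at rejected doses for the Wilson intervals and the hierarchical model.
- The sample size at those doses depends on outcome, so the raw normalisation rate at a stopped dose is biased downward and should be reported with that caveat.
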